#### Missing data

Although attempts will be made to minimize missing data, we anticipate that some data will be missing despite these efforts because of participant attrition and non-response. We will explore patterns of missing data to determine whether the missingness is at random. We will consider data that are Missing at Random (MAR) to be explained by observed covariates. If we believe that missingness is due to unobserved factors (MNAR—Missing Not at Random), then we will use selection models to identify variables to explain it, or pattern mixture modeling. We will examine whether the results of sensitivity analyses are similar with and without missing data adjustments.

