#### Sample size and power

This randomized trial aims to enroll up to 700 young women, with an expected enrollment of 600 based on the power calculation for the study design. We used the Stata command *sampncti* [36], which is based on the equation developed by Chow, Shao, and Wang [37] to calculate the detectable difference in primary outcomes between participants in the control arm and participants in the face-to-face YWC arm. We hypothesize that the participants in the face-to-face YWC arm and participants in the mHealth YWC arm would not have statistically significant different primary outcomes at 6 months; therefore, we calculated the detectable difference based on the control and face-to-face YWC arms. Our parameters were based on a sample size that is feasible given the study design (*n* = 600; 200 participants per arm; an average of 67 participants per condition per county), three counties per arm, intraclass correlation (ICC) = 0.10, and alpha = 0.05, and a two-sided test. All outcome estimates are based on the principal investigator’s (PI’s) previous studies conducted with key populations of young women who use substances in North Carolina [31] and in South Africa [38].

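### The missing-data rule claims to establish MAR from observed patterns and commits to MNAR models only if the team comes to believe they are needed

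*Protocol article*

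**What the plan says.** Everything relevant is in the Missing data section of the protocol article. It expects loss: "we anticipate that some data will be missing despite these efforts because of participant attrition and non-response". It gives no rate. It then sets out a sequence.

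- Classification: "We will explore patterns of missing data to determine whether the missingness is at random".
- If MAR: "We will consider data that are Missing at Random (MAR) to be explained by observed covariates".
- If MNAR: "If we believe that missingness is due to unobserved factors (MNAR—Missing Not at Random), then we will use selection models to identify variables to explain" the missingness, with pattern-mixture modelling named as the alternative.
- Closing check: "We will examine whether the results of sensitivity analyses are similar with and without missing data adjustments".

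The section makes no commitment to an MNAR analysis that would be run regardless of how the missingness is classified.

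**The concern.** MAR and MNAR differ in whether, given what was observed, the chance of being missing still depends on the unseen outcome. The observed data carry no information on that without further assumptions that cannot be tested. The section nevertheless treats the distinction as something that exploration can settle, and makes the MNAR models conditional on the answer.

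The consequence runs in one direction. If the patterns look harmless and the team concludes MAR, the text commits to no analysis that allows the missing women to differ from similar women who returned. Yet a harmless-looking pattern is fully compatible with MNAR.

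In this trial such loss is plausible, although that is inference and not something the article says. The primary outcomes include self-reported condomless sex and substance use (Outcomes). The retention procedures plan for women who change contact details or lose their housing (Retention). The arms also differ in scheduled contacts: three, four and five for HCT, mHealth and face-to-face (Participant timeline). Loss could be related to outcome, and could differ by arm.

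A second fault lies in the description of the MNAR method, "selection models to identify variables to explain it, or pattern mixture modeling". A selection model does not search for explanatory variables. It assumes a form for the link between dropout and the unseen outcome, and the data cannot verify that link.

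**Working it through.** The plan prints no attrition rate, detectable difference or missing-data figure, so there is no stated result to reproduce. The only related figures are the sample sizes in Sample size and power, "200 participants per arm; an average of 67 participants per condition per county". They agree with each other: 3 × 200 = 600, and 200 / 3 = 66.7, or about 67.

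**Step 1. Can observed patterns decide between MAR and MNAR?** Two large simulated two-arm data sets (400,000 records) were built from the same covariate, the same arm labels and the same missingness indicator, which depended on the covariate. About 19% of outcomes were missing. In the first set, the missing outcomes followed the same model as the observed ones (MAR). In the second, the missing outcomes in one arm were lowered by 0.5 SD (MNAR).

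| | MAR set | MNAR set |
|---|---|---|
| Observed outcomes | identical | identical |
| Arm difference among observed | −0.001 SD | −0.001 SD |
| Arm difference in full data | −0.003 SD | −0.099 SD |

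The gap between the two full-data differences is what the formula in step 3 predicts: 0.193 × 0.5 = 0.097 SD. Any exploration of the observed data gives the same answer for both sets, so it cannot tell which one is in hand.

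**Step 2. Is the section consistent with its own definitions?** It takes MAR to be missingness accounted for by observed covariates, and MNAR to be missingness due to unobserved factors. For the MNAR case it then proposes to find variables that explain the missingness. If measured variables do explain it, the data are MAR by the section's own definition. If they do not, the proposed search has nothing to find.

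**Step 3. How large could an unexamined bias be?** Let m be the missing fraction in an arm and δ the amount, in SD, by which its missing outcomes depart from the MAR prediction.

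Bias in the arm difference = m₁δ₁ − m₀δ₀

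With the same m in both arms this is m × (δ₁ − δ₀). Neither m nor δ is in the document. The values below are assumptions. With 200 women per arm, 10–30% missing means 0.10 × 200 = 20 to 0.30 × 200 = 60 women.

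| Missing fraction | δ₁ − δ₀ = 0 | 0.2 SD | 0.5 SD |
|---|---|---|---|
| 10% | 0 | 0.02 | 0.05 |
| 20% | 0 | 0.04 | 0.10 |
| 30% | 0 | 0.06 | 0.15 |

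**Step 4. Does the closing comparison fill the gap?** Setting adjusted beside unadjusted results varies whether an adjustment is made. It varies the assumption about the unseen outcomes only if one of the adjustments is itself an MNAR model, and the preceding sentence makes those models conditional. At best the closing sentence is ambiguous on this point.

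**The case against.** **The judgement may not rest on patterns alone.** The MNAR trigger is a belief, and the section does not say that only observed patterns may inform it. Subject-matter knowledge, or what staff learn while tracing participants, could contribute, and that would be legitimate. Exploring patterns is also sound practice; the fault lies in claiming that it determines the mechanism. This stands as a limit on how rigidly the rule should be read. It does not rescue the conditional commitment, since no source of belief makes MAR certain.

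**The closing sentence may include MNAR models.** It is not conditional, and it does not say that the unadjusted analysis is complete-case or that the adjustments assume MAR. A reader might infer a plain complete-case versus MAR comparison, but the text does not say so. What remains is that it does not guarantee an MNAR analysis.

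**This is a condensed article.** The choice between the two MNAR families, the trigger criterion, the imputation covariates and the shift values commonly belong to the SAP. That is correct, and none of them is raised as missing here. The point concerns what the article states: the claim to determine MAR, the conditional use of MNAR models, and the account of selection models.

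**The size is assumed.** This is also correct. Reasons for loss such as continued substance use or unstable housing are not specific to one arm. Equal missingness and equal departures would cancel. Baseline substance use and victimization are measured (Eligibility criteria), so part of any such loss may be accounted for under MAR.

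**A stronger reading that fails.** A reader might infer that the method will be chosen with the treatment effect in view, and so charge the plan with result-driven analysis and inflated type I error. The section ties the choice to missingness and its believed cause, never to the estimated effect, and does not say what is known when the choice is made. What can be said is that the choice rests on a judgement made from accrued data. A type I error figure would require an assumption of selective reporting that the article does not propose.

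**Conclusion.** The concern holds in a limited form. The stated rule claims to settle from observed patterns something they cannot settle, and makes MNAR analysis conditional on that judgement. The team could follow the article exactly, conclude MAR, and run no MNAR sensitivity analysis. The description of selection models is also wrong.

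The possible cost is an unexamined bias of 0.02–0.15 SD in an arm comparison, given 10–30% missing and a difference between arms of 0.2–0.5 SD in departure from MAR. All of these inputs are assumptions, and the bias is zero in the symmetric case. The article prints no detectable difference, so the bias cannot be expressed as a share of the design effect. No sample-size figure is affected.

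This should be corrected. It is a fault in how robustness is planned and does not show that the main comparison is biased.

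**What to change.** Replace the conditional rule with three statements.

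1. Patterns of missingness will be described by arm, county, cycle and baseline characteristics, with no claim that this determines MAR.
2. The primary analysis assumes MAR, through a likelihood-based model or multiple imputation, and uses all enrolled women and the baseline data already collected.
3. One pre-set MNAR sensitivity analysis will be run whatever the patterns show. An example is a delta-adjusted pattern-mixture analysis with shifts set separately by arm, including equal shifts, and reporting the shift at which the conclusion changes.

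If selection models are kept, describe them as assuming a link between dropout and the unseen outcome. Say in the closing sentence which analyses are to be compared.

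This will not remove an MNAR bias; it will show how large a departure from MAR would be needed to change the conclusion. The cost is wording and a few extra model runs, with no new data collection. The article gives the trial status as enrolling, so on that timeline the change can be made before the final data are in.

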#### Data monitoring

A Data and Safety Monitoring Board (DSMB) has been convened to protect the safety of participants and ensure the integrity of collected data. The DSMB meets biannually and is composed of three professionals with expertise in adolescent health and medicine, bioethics and women’s reproductive health, and statistics and research methods, respectively. This board is independent from the researcher and the sponsoring institution for the study. DSMB members discussed whether stopping rules were necessary for this study and they determined that these rules were not necessary.

#### Reporting of adverse events

Because this study presents minimal risk to study participants, study-related adverse events (AEs) or serious adverse events (SAEs) are unlikely. In the rare event that study-related AEs or SAEs occur, staff are directed to immediately notify the project director and PI or designee (a trained clinical psychologist) and submit SAE and incident reports. The PI will report SAEs within 48 h to the National Institute on Drug Abuse (NIDA), RTI’s Office of Research Protection, and the DSMB chair, with a follow-up report submitted within 72 h after initial reporting. The PI will report SAEs to the NIDA Project Officer within 48 h of the event by e-mail. A written follow-up will be sent within 72 h of the event. Additionally, AEs and SAEs will be reported to RTI’s IRB and in reports to the DSMB.

### Ethics and dissemination

The experimental phase of the study received approval from the RTI Committee for the Protection of Human Subjects in August 2016. In addition, research committees of Wake County Human Services and the Durham County Department of Public Health reviewed the study and all related materials with each organization, granting full study approval in November 2016. The Guilford County Department of Public Health Director granted approval in lieu of a formal review by a research committee. All site-based project staff have to complete RTI’s basic human subjects research training module upon hire and before initial contact with any potential study participants. This training will be repeated annually. Furthermore, all staff members responsible for data collection have signed Staff Agreements of Confidentiality to pledge that they will ensure confidentiality of participants and study data. The study findings will be disseminated through our established Community Collaborative Board, program newsletter, journal articles, conference presentations, websites, and targeted dissemination meetings.

## Discussion

HIV among African American women remains disproportionate compared with other racial/ethnic groups of women, especially in the southern United States. It is critical to engage young African American women in the HIV care continuum. This randomized trial seeks to test the efficacy of two formats of the YWC—one is an innovative mHealth delivery and the other is face-to-face delivery—relative to standard HCT. A woman-focused intervention delivered via an mHealth app may be appropriate, especially when adapted for this 18- to 25-year-old population. If this format is found to be efficacious, an mHealth app may succeed in expanding the reach of the HIV risk-reduction intervention, making the YWC more accessible to young women who use mobile devices.

### Trial status

Enrolling.

## Abbreviations

AE: Adverse event
AOD: Alcohol or other drugs
CDC: Centers for Disease Control and Prevention
DSMB: Data and Safety Monitoring Board
GBV: Gender-based violence
HBCU: Historically black college or university
HCT: HIV counseling and testing
HIV: Human immunodeficiency virus
ICC: Intraclass correlation
IPV: Intimate partner violence
IRB: Institutional review board
NIDA: National Institute on Drug Abuse
NIH: National Institutes of Health
PHIT: Personal Health Intervention Tool
PIN: Personal identification number
RTI: RTI International
SAE: Serious adverse event
STI: Sexually transmitted infection
WC: Women’s CoOp
YWC: Young Women’s CoOp
